#### Secondary Aims

The same analyses, significance tests, sharp null hypothesis, and result reporting described for the primary aim will be used to assess aim 2, the effect of CM versus CL on module-specific target outcomes. The model-specific target outcomes are presented in Table 1. Using regressions (linear if no outliers and quantile if outliers), adjusted differences between CM and CL in module-specific outcome scores will be assessed after each module and at the intervention end point (T_4_) adjusted for the score before completing the module.

If intervention effects are observed on the DERS-SF, aim 3 will involve conducting mediation analyses to assess whether greater improvements on the DERS-SF (primary outcome), in the CM versus CL condition, mediate the effects of CM versus CL on anxiety and depression symptoms (secondary outcomes).

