#### Screening and Initial Phone Call

Consenting participants are automatically redirected to a web-based screening survey to assess eligibility. Subsequently, eligible participants complete the baseline survey and are telephoned to administer the Mini International Neuropsychiatric Interview (MINI) [45] and conduct a risk assessment. Individuals deemed high risk (ie, probable risk of harming themselves) are excluded over the phone and referred to relevant psychiatric services. Eligible participants are randomized to either CM or CL. This group allocation and a summary of their intervention are conveyed to participants over the phone.

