#### Treatment Group: CM

CM is a web-based version of the UP’s Transdiagnostic Treatment for Emotional Disorders [15]. The overall goal of the UP is to help individuals understand and recognize their emotions and respond to uncomfortable emotions in a more adaptive manner. Participants allocated to CM receive four UP-adapted modules titled (1) understanding emotions, (2) mindful emotion awareness, (3) flexible thinking, and (4) doing things differently. CM is a reduced format of the UP, as 2 core UP modules (modules 6 and 7) have been excluded from CM owing to their sole focus on exposure therapy, which was deemed inappropriate for remote delivery for individuals experiencing chronic health conditions. In CM, each module comprises 14 daily activities on the web (3-10 minutes each), which allow participants to apply what they have learned from the psychoeducational readings and videos. Participants are not expected to complete *every* daily activity, although they must complete at least 1 to 2 core activities per module before they could move on to the subsequent module. This format aims to mirror a more real-life, clinician-led intervention, where clients would not prematurely progress to a subsequent and more advanced module without first being exposed to fundamental skills from the previous modules (ie, in CM, participants must first learn about what an emotion is [module 1] before they can begin to mindfully engage with their emotional experiences [module 2] and change them [modules 3 and 4]). As a result, participants who reach the end of the entire intervention have been exposed to all core skills. Each module is outlined in subsequent sections, and a summary overview is provided in Table 1.

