#### Primary Aim

Missing data are ubiquitous in research, and dropout and incomplete data (eg, dropout) are particularly common in web-only trials [62]. For aim 1 analyses, we will address missing data using multiple imputation with a fully conditional specification [63] and predictive mean matching [64]. A total of 20 imputed data sets will be generated. The primary outcome of the trial is the Difficulties in Emotion Regulation Scale (DERS-SF). The primary end point is immediately after the intervention, immediately following module 4 (T_4_). Anxiety and depression symptoms as well as overall QoL are secondary outcomes. All outcomes are continuous measures.

The primary analyses will consist of linear regressions on multiple imputed data. Each outcome variable at the primary end point (T_4_) will be included as the outcome variable in a linear regression, with group as the main predictor and the outcome variable at baseline (T_0_) and stratification factors included as covariates. Adjusted means in each group, as well as the adjusted mean difference, will be calculated. In the event of outliers, quantile regression will be used in place of linear regression and adjusted median differences at the primary end point (T_4_), and as exploratory analyses, the other time points will be estimated. Following recent research suggestions [65], we chose to provide randomization-based inferences; that is, statistical significance will be based on Fisher exact *P* values [66] from 100,000 permutations for the adjusted mean differences and uncertainty intervals will be based on 95% Fisher intervals. The sharp null hypothesis tested will be that being randomized to CM has an identical effect on participants’ outcomes as being randomized to CL.

Given the conceptual overlap between stratification factors and the outcome measured at baseline, only the stratification factors for anxiety and depression will be included in the linear regression assessment of the primary outcome (DERS-SF). For the linear regression assessment of depression and anxiety symptoms, only the DERS-SF stratification factor will be included. For the linear regression assessing QoL, both stratification factors will be included.

In addition to testing for group differences at the primary end point (T_4_), we will explore group differences at T_1_, T_2_, T_3_, and T_5_ on the primary and secondary outcomes. The overall sample mean at T_0_ will be presented for comparison.

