### Strengths and Significance

Despite these limitations, this is the first randomized controlled trial to evaluate an emotion-focused, UP-adapted, and internet-delivered intervention designed for cancer survivors to improve their mental health and QoL. Considering (1) that most of those diagnosed with cancer survive their diagnosis [68], (2) that cancer survivors experience elevated symptoms of psychological distress and lower QoL [1,36], and (3) that cancer survivors may face economic and geographic barriers to accessing mental health support [21,23,69], the development of web-based and affordable interventions that are highly accessible is paramount. Finally, as CM is internet-guided, it is also expected to have a low therapist burden and is considered highly scalable.

Another strength of this study relates to its unique study design. The trial will allow not only an assessment of symptom improvement but also an evaluation of factors that account for symptom changes. Specifically, by concurrently measuring emotion regulation and psychopathological symptoms at all time points, the design will enable the assessment of more nuanced relationship patterns between these closely linked variables. Thus far, few studies assessing applications of the UP have been able to clearly decipher whether improvements in emotion dysregulation are truly mediating symptom improvements.

Furthermore, the study will allow a detailed assessment and comparison of each module’s effects in the treatment versus control conditions. This mechanistic analysis allows for greater treatment optimization. For example, if the target outcome of one module is found to contribute minimally compared with the other modules, then theoretically, the less effective module may be removed or decreased in intensity to reduce intervention duration and improve treatment efficiency.

In addition, the CL intervention material may prove to be a rather formidable control comparator. This is because lifestyle factors, such as diet [70], exercise [71], relaxation [72], and sleep [73], are highly correlated with mental health outcomes. Therefore, if CM is more efficacious than CL in improving emotion regulation and anxiety and depressive symptoms, such findings will speak to the strength and magnitude of the effects of CM.

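### Aim 2 adjusts the comparisons for modules 2 to 4 for a post-randomization score, so if earlier modules moved the target the result is neither the randomized CM versus CL effect nor a clean module effect

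*Protocol article*

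**What the plan says.** Protocol article, Statistical Analysis Plan, Secondary Aims, opens Aim 2 by carrying over the Aim 1 machinery: "The same analyses, significance tests, sharp null hypothesis, and result reporting described for the primary aim will be used to assess aim 2". It presents this as the effect of CM versus CL on the module-specific targets. It then sets a different covariate. The arms are compared on each target scale once the module is over "and at the intervention end point (T_4_) adjusted for the score before completing the module".

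Under Primary Aim, the Aim 1 regressions use "the outcome variable at baseline (T_0_) and stratification factors included as covariates". The null carried over to Aim 2 is stated there too: "The sharp null hypothesis tested will be that being randomized to CM has an identical effect on" outcomes as randomization to CL. It concerns the arms, not any one module.

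On timing, Screening and Initial Phone Call says that "eligible participants complete the baseline survey and are telephoned to administer the Mini International Neuropsychiatric Interview", and randomization follows. Table 3 lists every target scale at T0 to T5. Assessment Time Points and Measures says that a module cannot start until the preceding postmodule survey is done.

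On use, the Aims section heads Aim 2 as exploratory and asks about the role of each module. Strengths and Significance adds that "if the target outcome of one module is found to contribute minimally compared with the other modules", that module could in theory be taken out or made lighter. Neither Sensitivity Analyses nor Limitations mentions the timing of the covariate.

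**The concern.** A regression on a covariate that treatment may already have changed no longer estimates the effect of randomization. Aim 2 asks two things: whether CM changes the target outcomes, and what each module contributes. The first needs a contrast adjusted only for pre-randomization scores, and Secondary Aims specifies none for the targets of modules 2 to 4. The second needs earlier gains to be separated from new ones, and a regression on the preceding survey does that only under a particular pattern of persistence. A module could look useful because of what came before it, or look weak because an earlier gain faded. The protocol suggests using such results to redesign the programme.

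**Working it through.** The protocol states no figure for Aim 2, so there is nothing to reproduce. The check is on what the planned coefficient estimates.

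**Inputs**
- *b*, the within-arm slope of post-module on pre-module score (equal to the correlation when SDs are equal). Power Analysis uses 0.3 to 0.6, but for baseline to postintervention. No value is given for surveys one module apart, so 0.8 and 0.9 are added as assumptions.
- *D*, the arm difference on the target already present before the module. Not given; 0.5 SD and 0.25 SD are assumed.
- *p*, the share of *D* still present at the post-module survey. Not given; *p* = 1 is the main case and others follow.
- *N* = 100 (Power Analysis) and 61 + 75 = 136 (Results, T4 completers).

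**Step 1: which score is the covariate**

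| Module | Target scale | Covariate | Timing |
|---|---|---|---|
| 1 | BES | T0 | before randomization |
| 2 | SMQ | T1 | after |
| 3 | CERQ, UP-CSQ | T2 | after |
| 4 | MEAQ-30 | T3 | after |

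Module 1 is unaffected.

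**Step 2: the coefficient.** The adjusted group difference is (post difference) − *b* × (pre difference). If the module adds *m*, the post difference is *pD* + *m*, so

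coefficient = *m* + (*p* − *b*) × *D*.

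**Step 3: an inert module (*m* = 0) with full persistence (*p* = 1).** The credit is (1 − *b*) × *D*.

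| *b* | Credit, *D* = 0.5 | Simulated, N = 100 | t test P<.05, N = 100 | t test P<.05, N = 136 | Credit, *D* = 0.25 |
|---|---|---|---|---|---|
| 0.3 | 0.35 | 0.356 | 43% | 53% | 0.175 |
| 0.4 | 0.30 | 0.299 | 34% | 44% | 0.150 |
| 0.5 | 0.25 | 0.247 | 27% | 38% | 0.125 |
| 0.6 | 0.20 | 0.198 | 22% | 28% | 0.100 |
| 0.8 | 0.10 | 0.101 | 12% | 15% | 0.050 |
| 0.9 | 0.05 | 0.050 | 9% | 12% | 0.025 |

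At *D* = 0.25 and N = 100, rejection is 14% at *b* = 0.3 and 9% at *b* = 0.6.

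**Step 4: other persistence.**
- No spillover (*D* = 0): credit 0.
- *p* = *b*: credit 0. With *D* = 0.5 the simulated values ran from −0.005 to 0.003, with rejection of 4% to 6%.
- *p* < *b*: negative. For example, (0.4 − 0.6) × 0.5 = −0.10 SD.
- Measurement error: if the gain fades at the same rate φ as the underlying trait, then *p* = φ and *b* = φ × reliability, so the credit is φ × (1 − reliability) × *D*. With *D* = 0.5 this is 0.05 (φ = 1, reliability 0.9), 0.10 (φ = 1, reliability 0.8) and 0.035 (φ = 0.7, reliability 0.9). Simulation gave 0.049, 0.101 and 0.033. The protocol gives a reliability only for the DERS-SF (0.90), none for the target scales.

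**Step 5: the randomized effect.** The cumulative arm effect after the module is *pD* + *m*; the coefficient falls short of it by *bD*. With *p* = 1, *m* = 0 and *D* = 0.5, the randomized effect is 0.50. The coefficient is 0.20 at *b* = 0.6 (0.30 removed) and 0.05 at *b* = 0.9 (0.45 removed). A higher correlation therefore shrinks the false module credit but removes more of the randomized effect.

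**Step 6: the test.** A permutation test of the adjusted difference (N = 100, 999 permutations) rejected in 4%, 6% and 5% of trials at *b* = 0.3, 0.6 and 0.8 when no module did anything. For an inert module inheriting 0.5 SD it rejected in 45%, 23% and 15%. The test is behaving correctly: once an earlier module has worked, the null that CM and CL are identical is false. The simulations leave out imputation and the stratification factors.

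**The case against.** The strongest reply is that every figure above is conditional. Background describes each module as aimed at a distinct skill, and Table 1 gives each its own scale, so large spillover cannot be taken for granted. An inherited 0.5 SD equals the smaller SMD used to power the whole package, here assigned to modules that do not target the scale. Surveys one module apart may correlate above 0.6. All of this stands. A reader might infer that the plan will credit an inert module with 0.20 SD, or find one significant in 28% of trials. The documents do not support that as a forecast; those values belong to one set of assumptions. Some positive credit is nonetheless plausible: the modules are described as cumulative, and questionnaire error pulls the slope below true persistence.

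A reader might also infer that differencing successive T0-adjusted contrasts would isolate a module. It gives an inert module −(1 − *p*) × *D*, which is zero only under full persistence. With φ = 0.8, reliability 0.9 and *D* = 0.5 (all assumed), differencing gives −0.10 SD, while the planned regression gives 0.8 × 0.5 × 0.1 = +0.04 SD. A plain change score also has variance 2(1 − r) against 1 − r²: 25% larger at r = 0.6 and 54% larger at r = 0.3. Neither method dominates, so differencing is no replacement.

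Three further inferences fail. The remark on removing modules is hypothetical and sits in the discussion; it is not a decision rule. Nothing in the document shows that dropout biases these comparisons, and the argument here does not depend on it. The Aim 1 analyses are untouched.

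Finally, the pre-module score could be read as T0 throughout. The survey schedule, and the explicit T0 in Primary Aim, make that unlikely; if it is what was meant, the sentence needs correcting.

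**Conclusion.** The point holds as a should-fix matter for an exploratory aim. That the covariate for modules 2 to 4 is post-randomization follows from the text and needs no assumption. That the coefficient misses both the randomized effect and the module effect requires earlier modules to have moved the later target; the document gives no figure for this. The direction then depends on persistence against the within-arm slope: over-credit if the gain outlasts the slope, none if they match, under-credit if it fades faster. For a fully persisting 0.5 SD, the range is 0.35 SD down to 0.05 SD over slopes 0.3 to 0.9, and half of that for 0.25 SD. A significant result for a later module shows that the arms differ, not that the module worked.

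**What to change.** In Secondary Aims, make the main Aim 2 result, for every module-specific outcome, the CM versus CL contrast at each of T1, T2, T3 and T4, adjusted for the T0 score and the stratification factors. Describe it as the cumulative effect of CM versus CL up to that survey. The planned permutation test and sharp null fit this contrast as they stand.

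Keep the regression on the pre-module score as a descriptive analysis of module increments. If wanted, add the difference between successive T0-adjusted contrasts beside it. State that each relies on an assumption about how earlier gains persist.

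In Strengths and Significance, add that with a fixed module order these estimates alone cannot justify removing or shortening a module.

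Cost: wording and a few extra models on data already collected. Counting the two CERQ subscales separately there are six target scores, so 6 × 4 = 24 regressions, reported as exploratory. The price is a more cautious module-level interpretation.

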One cognitive-behavioral intervention designed to target approach-oriented emotion regulation is the Unified Protocol (UP) [15]. The UP is considered transdiagnostic as it effectively improves emotional distress, including symptoms of anxiety and depression, across a range of psychopathologies [16]. Furthermore, pilot studies have demonstrated that the UP may improve depressive symptoms and emotion regulation among people with breast cancer [17]. This suggests that the UP may be effectively adapted for oncological populations. On the basis of these findings, we recently developed the CanCope intervention, an internet-delivered adaptation of the UP’s modules, tailored to the needs of cancer survivors of any diagnosis. Each CanCope module was assessed independently in a series of pilot trials. Our results suggested high feasibility, participant satisfaction, and preliminary efficacy of each independent module in improving emotion regulation and mental health symptoms when delivered remotely [18]. These are promising preliminary findings, given that accessibility to face-to-face mental health support for oncological populations is often comprised of geographic location, financial strain, lack of available health care personnel, the iatrogenic effects of cancer treatments, and more recently the COVID-19 pandemic [1,19-24]. This inequality in care indicates the need for evidence-based, remotely delivered, and scalable psychological interventions for cancer survivors.

Although many psychological interventions target the mental health of patients with cancer and cancer survivors [25-27], few have examined the potential underlying mechanisms. This is not specific to psycho-oncology; the lack of well-designed mechanistic research is widespread across intervention research [28,29]. Overall, there is a lack of understanding around *why* and *how* interventions achieve their desired effects. For instance, meta-analytic findings reveal that even though the UP may be effective in improving symptom outcomes, there is a lack of evidence to suggest that these effects are mediated through changes in emotion regulation [16].

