#### Aim 3

If the CM intervention improves emotion dysregulation, we will assess whether changes in emotion dysregulation mediate the effects of CM versus CL on anxiety and depressive symptoms. Hypothesis 2 states that improvements in anxiety and depressive symptoms for CM compared with CL participants —after the treatment will be mediated by greater reductions in emotion dysregulation in CM participants than in CL participants.

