### Statistical Analysis Plan

#### Power Analysis

The primary end point for the trial is the immediate postintervention assessment (T_4_). As all primary and secondary outcomes are continuous, the primary analyses will be linear regressions with group as a predictor and outcome scores at baseline included as a covariate. We set the type 1 error at Cronbach α=.05 (2-tailed). A Monte Carlo simulation study was conducted to determine the power analysis and required sample size. In the simulation, we varied (1) the correlation between baseline and postintervention outcome scores (*r*) across four values (0.3, 0.4, 0.5, and 0.6) selected from the literature and our pilot research [18] and (2) the standardized mean difference (SMD) between the CM and CL groups at post intervention on outcome scores (primary end point) across 2 values (SMDs of 0.5 and 0.6). The SMDs were selected based on our pilot work [18] where we observed SMDs from before to after the intervention of approximately 0.5 to 1.0 for our primary and secondary outcomes. Our pilot did not include a control group (likely inflating the SMDs) but only tested individual modules separately (likely reducing the SMDs); therefore, we believe that a moderate SMD was reasonable, on average. The code for this Monte Carlo study is publicly available [61]. Results from 10,000 Monte Carlo simulations for each of the conditions and varying sample sizes showed that participants (n=100) with complete data at T_4_ will provide more than 80% power to detect a medium (SMD=0.5) group difference—after the intervention, even with only a moderate correlation (*r*=0.3) between baseline and postintervention outcome scores with Cronbach α=.05.

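### Running the aim 3 mediation analysis only after a DERS-SF effect is observed biases the reported indirect effect away from zero (slightly at the planned effect, markedly at smaller ones) and leaves no estimate when the condition fails

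*Protocol article*

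**What the plan says.** The condition appears twice. The third aim in the introduction reads: "If the CM intervention improves emotion dysregulation, we will assess whether changes in emotion dysregulation mediate the effects of CM versus CL"; the outcomes meant are the two symptom scores. In the Statistical Analysis Plan, under Secondary Aims: "If intervention effects are observed on the DERS-SF, aim 3 will involve conducting mediation analyses". Hypothesis 2 states that the symptom gains of CM over CL "will be mediated by greater reductions in emotion dysregulation in CM participants than in CL participants".

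The article does not say what counts as an observed effect. The nearest rule is the one for aim 1, where "statistical significance will be based on Fisher exact *P* values [66] from 100,000 permutations", with type 1 error of .05 and two-sided tests. The Sensitivity Analyses section lists four analyses, and none is a mediation analysis run without the condition.

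The mechanism question is presented as a main reason for the trial. The Background says of the Unified Protocol that "there is a lack of evidence to suggest that these effects are mediated through changes in emotion regulation". Strengths and Significance says that "few studies assessing applications of the UP have been able to clearly decipher whether improvements in emotion dysregulation are truly mediating symptom improvements".

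**The concern.** An indirect effect is the product of two paths: treatment to mediator (a) and mediator to outcome (b). Here a is the CM-CL difference on DERS-SF. If the product is computed only in trials where the estimate of a came out large enough, the sampling distribution of a is truncated from below and the average reported product exceeds the true one.

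The condition also decides whether an estimate exists at all. A DERS-SF difference that misses the threshold is not a zero difference, yet no indirect effect would then be planned. That includes the result of most interest against Hypothesis 2, in which anxiety or depression improves and DERS-SF does not clearly move. At stake are the size and the completeness of the mediation result for a secondary aim that has its own hypothesis. The primary comparison is not touched.

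**Working it through.** **Inputs from the article.** T4 completers: 61 CM and 75 CL (Results). Baseline-to-post correlation r: 0.3 to 0.6; planned SMD: 0.5 and 0.6; planned completers: 100 (all Power Analysis). Two-sided 5% test of a baseline-adjusted difference (Power Analysis; Primary Aim).

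**Assumptions not in the article.** *Observed* means two-sided P<0.05 in CM's favour at T4. Completers only, although aim 1 uses multiple imputation. SMDs are in units of the unadjusted SD. True SMDs below 0.5 are shown as a range.

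**The plan's own figure.** At the design effect, the chance that the condition is met equals the power of the DERS-SF test. The article states more than 80% for 100 completers, SMD 0.5 and r=0.3. I get 74.6% (normal) or 73.7% (t), so that figure does not reproduce on a two-sided test with 50 per arm. This is a separate matter and does not drive the present point.

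**Formulas.** With SE = √[(1 − r²)(1/61 + 1/75)] and critical value 1.978 (133 degrees of freedom):

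- threshold c = 1.978 × SE
- k = (c − d)/SE
- P(condition met) = 1 − Φ(k)
- mean estimate given the condition is met = d + SE × φ(k)/[1 − Φ(k)]
- inflation = that mean divided by d

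**Worked at r=0.3.** SE = √(0.91 × 0.02973) = 0.1645 and c = 0.325.

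- SMD 0.5: k = −1.06; met in 85.6%; mean 0.5 + 0.1645 × 0.227/0.856 = 0.544; inflation 1.09.
- SMD 0.3: k = 0.154; met in 43.9%; mean 0.3 + 0.1645 × 0.394/0.439 = 0.448; inflation 1.49.

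**Results for 61 v 75 completers, r from 0.3 to 0.6.**

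| True SMD on DERS-SF | Condition fails | Inflation of a |
|---|---|---|
| 0.6 | 5% to 1% | 1.03 to 1.01 |
| 0.5 | 14% to 5% | 1.09 to 1.03 |
| 0.4 | 33% to 18% | 1.22 to 1.11 |
| 0.3 | 56% to 42% | 1.49 to 1.31 |
| 0.2 | 78% to 70% | 2.10 to 1.80 |

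With 50 v 50, SMD 0.5 and r=0.3, the condition fails in 26% and the inflation is 1.17.

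**Does it carry through to the product?** Simulation with b = 0.5 and no direct effect (both assumed), 61 v 75, r=0.3, 10,000 trials per setting. Signs are set so that benefit is positive.

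| True SMD | True indirect effect | Mean, always run | Mean, condition met | Mean, condition failed | Both paths significant, without / with condition |
|---|---|---|---|---|---|
| 0.5 | 0.250 | 0.250 | 0.272 | 0.123 | 0.850 / 0.850 |
| 0.3 | 0.150 | 0.151 | 0.225 | 0.093 | 0.440 / 0.440 |

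The mean b stayed at about 0.50 in the selected trials, so all the inflation comes from a. Always running the analysis gives an unbiased mean. The estimates that would go unreported are below the truth but not zero. With no DERS-SF effect (30,000 trials), both paths were significant in 4.8% of trials without the condition and 2.3% with it, because the condition admits only results in CM's favour. It does not raise type I error.

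**The case against.** The case for leaving the plan alone has real force. The condition is prespecified, and letting a mechanism analysis follow an effect on the primary outcome is a conventional choice. Removing it does not change the joint-significance test when there is an effect. At the SMDs of 0.5 and 0.6 that the plan uses, the inflation with the actual completers is below 10%. The larger figures need a true effect that the Power Analysis did not consider. Conventional interval coverage for a is also little disturbed there: about 97% at SMD 0.5 and 94% at 0.3 in the simulated trials that met the condition (r=0.3). *Observed* may be meant more loosely than P<0.05, and a full analysis plan that is not shown may define it. A lower threshold gives less bias, in the same direction. All of this stands, and it limits the weight of the point.

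Two stronger readings are tempting and are not supported.

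- A reader might infer that the trial can report only mediation or no result on mediation. It can report more. The condition selects on a and leaves b alone. In a simulation with 61 v 75, r=0.5, a DERS-SF SMD of 0.5, a direct symptom effect and no path from DERS-SF to symptoms, the condition was met in 91% of trials, the indirect effect averaged 0, and b was significant in 5%. And if the condition fails, the Primary Aim section still gives adjusted differences and 95% Fisher intervals for DERS-SF, anxiety and depression, which bear on Hypothesis 2.
- A reader might infer that any reported indirect effect will be seriously inflated. That depends on the true effect, and at the planned one the inflation is slight.

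What the objection does not remove is that a failed condition leaves the indirect effect and its interval unestimated. Smaller true effects are also plausible on the article's own account: its SMD rests on uncontrolled pilots (with an offset claimed for testing modules singly), and it calls the comparator potentially formidable.

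**Conclusion.** The point holds as one of estimation and complete reporting for a secondary aim, and it is modest in size. If *observed* means two-sided P<0.05 in CM's favour, with 61 v 75 completers and r of 0.3 to 0.6, the reported indirect effect is inflated 1.03 to 1.09 times at a true SMD of 0.5 and 1.3 to 1.5 times at 0.3. No indirect effect is planned in 5% to 14% and 42% to 56% of trials respectively. These sizes rest on that reading, on completers rather than imputed data, and on a simple linear mediation model. The direction of the bias does not depend on the exact threshold. Neither the primary analysis nor the error rate is affected.

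**What to change.** Delete the condition under Aim 3 in the introduction and under Secondary Aims in the Statistical Analysis Plan. State instead that the indirect effect of CM versus CL through DERS-SF will be estimated and reported with its interval, for anxiety and for depression, whatever the DERS-SF result. If the authors want to keep the dependence, they can make a DERS-SF effect a requirement for claiming mediation rather than for running the analysis, and label the estimate accordingly when it is not met.

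The cost is a change of wording in two places, with no new data. The downside is that an imprecise indirect effect may have to be reported.
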